## Abstract

**Introduction:**

Delirium is a severe neuropsychiatric syndrome of rapid onset, commonly
precipitated by acute illness. It is common in older people in the emergency
department (ED) and acute hospital, but greatly under-recognised in these and
other settings. Delirium and other forms of cognitive impairment, particularly
dementia, commonly coexist. There is a need for a rapid delirium screening tool
that can be administered by a range of professional-level healthcare staff to
patients with sensory or functional impairments in a busy clinical environment,
which also incorporates general cognitive assessment. We developed the 4
’A’s Test (4AT) for this purpose. This study’s primary
objective is to validate the 4AT against a reference standard. Secondary
objectives include (1) comparing the 4AT with another widely used test (the
Confusion Assessment Method (CAM)); (2) determining if the 4AT is sensitive to
general cognitive impairment; (3) assessing if 4AT scores predict outcomes,
including (4) a health economic analysis.

**Methods and analysis:**

900 patients aged 70 or over in EDs or acute general medical wards will be
recruited in three sites (Edinburgh, Bradford and Sheffield) over 18 months. Each
patient will undergo a reference standard delirium assessment and will be
randomised to assessment with either the 4AT or the CAM. At 12 weeks, outcomes
(length of stay, institutionalisation and mortality) and resource utilisation will
be collected by a questionnaire and via the electronic patient record.

**Ethics and dissemination:**

Ethical approval was granted in Scotland and England. The study involves
administering tests commonly used in clinical practice. The main ethical issues
are the essential recruitment of people without capacity. Dissemination is planned
via publication in high impact journals, presentation at conferences, social media
and the website www.the4AT.com.

**Trial registration number:**

ISRCTN53388093;
Pre-results.

Strengths and limitations of this studyThe study protocol involved seeking a representative sample of older acute medical
patients in the emergency department and acute medical wards. A detailed,
structured reference standard with explicit and reproducible methods is used to
assess the features of delirium and reach a diagnosis.Two different rating scales, the 4 ‘A’s Test (4AT) and the Confusion
Assessment Method are being evaluated in similar groups of patients.Reference standard and index assessments were performed blinded to each other.A limitation of the study is that participants or legal proxies were required to
give consent and thus the sample was selected.

## Introduction

### Background

Delirium is a severe and distressing neuropsychiatric syndrome which is characterised
by acute deterioration in attention and other mental functions. The diagnostic
criteria are, in summary: a disturbance of consciousness (ie, reduced ability to
focus, sustain or shift attention) and a change in cognition. The mental status
deterioration develops over short periods of time (usually hours to days) and it
tends to fluctuate.^1 2^ Delirium is commonly
precipitated by acute illness, trauma or the side effects of medications. The
presence of a ‘medical condition’ is part of the Diagnostic and
Statistical Manual for Mental Disorders, fourth and fifth Edition (DSM-IV, DSM-5)
criteria. Delirium is extremely common: it affects at least 15% of patients in acute
hospitals and is more common in older people.^3–5^ It is independently associated with many poor outcomes.^6–10^ Delirium is also a marker
of current dementia^6 11^ and is associated
with acceleration of existing dementia.^12^ In
older patients without dementia, an episode of delirium strongly predicts future
dementia risk.^7 13^ The economic burden of
delirium derived from 2008 US data estimates the 1-year healthcare costs to be
$38–$152 billion,^13^ but there
are limited recent data on the costs associated with delirium.

Detection of delirium is essential because it indicates acute systemic or central
nervous system illness, physiological disturbance and drug intoxication or
withdrawal. Failure to detect delirium in the acute setting is associated with worse
outcomes.^14^ Specific management of delirium
is of obvious and immediate benefit to patients in many clinical situations,
for example, in reversing opioid toxicity, treatment of peripheral infections
which have presented with delirium, alleviating distress caused by delusions and
hallucinations^15^ and in prompting more
thorough assessment of symptoms.^16^

More broadly, detecting cognitive impairment in general (delirium, dementia,
depression, learning disability, etc) is a prerequisite for high-quality care because
of the multiple immediate implications of cognitive impairment for patients and
staff, including: ensuring adequate communication with patients and their families,
doing careful assessment of capacity to provide consent for clinical procedures,
avoiding giving treatments contrary to the law because of lack of consent,
alleviating distress more readily, avoiding unnecessary bed transfers and prompting
delirium prevention, including a detailed drugs review. Detection of dementia has
recently been highlighted in the Dementia Commissioning for Quality and Innovation
framework in operation in NHS England.^17^

In general medical and emergency department (ED) settings, delirium is grossly
underdetected: at least two-thirds of cases are missed.^5 18 19^ It is unclear why detection rates are so low.
Evidence from surveys and workshops has raised several possibilities, including
general ignorance about delirium, lack of awareness of its importance, uncertainty
about discriminating delirium from dementia and lack of time for assessment in the
acute setting.^20–24^ The
lack of a very rapid, simple and validated screening tool is a major factor in the
underdetection of delirium.

Many delirium assessment instruments have been developed that operationalise the
standard diagnostic criteria for delirium, but these have largely remained research
tools. The most commonly advocated screening tool for use in routine clinical care,
the short Confusion Assessment Method (CAM),^25^
has satisfactory sensitivity and specificity in trained hands though takes around
10 min to complete because it requires a cognitive assessment like the
Modified Mini-Cog^26 27^ to be done first.
The CAM also requires the rater to make subjective judgements of mental status.
Subjective judgements are less reliable, often more time-consuming and more difficult
for staff (particularly non-specialists) than simple objective measures with
clearly defined cut points.^27^

The problem of some patients being ‘untestable’ is likely to be another
important factor in delirium underdetection: many patients in acute settings are too
unwell, sleepy or agitated to undergo cognitive testing or even interview.^28–31^ Most screening tools do
not make explicit how these patients should be classified. The result is that mental
status assessments are often simply left uncompleted in most
‘untestable’ patients, and no diagnosis, and often no specific
treatment, is applied. This lack of diagnosis can be harmful.^14^

Finally, given the time pressures in acute settings, it is challenging to implement a
separate delirium screening instrument in addition to any existing general cognitive
screening instruments. The lack of a combined instrument allowing screening for both
general cognitive impairment and delirium may therefore contribute to the lack of
specific delirium detection. Early diagnosis of delirium using evidence-based
diagnostic tools offers a means for improved outcomes and more efficient resource
allocation decisions.

### Rationale for the study

Given the multiple constraints of the acute environment, the range of staff that
might be expected to screen for delirium, the common coexistence of delirium and
dementia and the heterogeneity of patients, we determined the requirements for a
screening tool (box 1).Box 1Requirements for a screening tool for delirium for use in the acute
hospital environmentShort (less than 2 min)Easy to learnEasy to administer and scoreCan be used by professional-level healthcare staff from a variety of
disciplinesAllows scoring of patients who are too drowsy or agitated to undergo
cognitive testing or clinical interviewTakes account of informant historyCan be administered through written questions to people with severe
hearing impairmentCan be administered to patients with visual impairmentsDoes not require subjective judgements based on interviewCombines delirium screening with general cognitive screeningDoes not need a quiet environment for administrationDoes not require physical responses such as drawing figures or clocks

There are multiple instruments for delirium screening, diagnosis, severity assessment
and monitoring.^32–35^ Before
deciding to design a new screening tool, we therefore examined each of the available
tools against the above criteria, focusing on screening tools such as the CAM. We
also searched the literature systematically, including conference proceedings, books
and book chapters, for any newly published tools as well as to examine the
study data for each tool. Most scales were excluded on grounds of duration alone. The
remaining scales lacked features such as general cognitive screening and other
important features. We thus found that, in late 2010, no existing tool fulfilled the
above requirements, and because of this we decided to design a new test. This
conclusion was supported by the National Institute for Health and Care Excellence
(NICE) Guidelines on Delirium^6^ which emphasised
the need for research on a screening tool for delirium suitable for routine use.

The subsequent design process involved scrutiny of each of the nearly 30 published
delirium assessment tools, evaluating the performance of each, including subtests, in
published studies and, in most cases, through direct clinical or research experience
of their use. Because we had decided to incorporate general cognitive screening into
the new instrument, to avoid the need to have separate instruments for cognitive
screening and delirium screening, we also reviewed the broader literature on brief
tests for general cognitive impairment (including dementia). In the context of
designing a screening tool for the acute hospital, it is important to note that
delirium generally causes cognitive impairment detectable on the kinds of tests used
for dementia screening.^36 37^ Therefore,
abnormal test results may indicate delirium and/or dementia (as well as other causes
of cognitive impairment, such as learning disability).

It is clinically essential to know if any such impairment is acute, that is,
delirium, but also important to identify underlying general (acute or chronic)
cognitive impairment. A tool designed exclusively to detect cognitive impairment will
not lead to delirium detection without another step, and a tool designed only to
detect delirium may miss general cognitive impairment. In this light, we decided that
the 4 ’A’s Test (4AT) should include cognitive screening
sensitive to general cognitive impairment, but also including items on altered level
of alertness and change in mental status, both of which are strong indicators of
delirium.

The first version of the 4AT was drafted and tested informally by colleagues, changes
were made based on feedback and updated versions were tested again. After
several iterations involving 20 doctors and nurses of varying levels of experience,
the final version was produced. An initial audit in 30 inpatients comparing clinical
use of 4AT with independent reference standard DSM-IV assessment found 100%
sensitivity (CI 69% to 100%) and 90% specificity (CI 68% to 99%). A subsequent
validation study in Italy involving 234 consecutively recruited older hospitalised
patients found that the 4AT had a sensitivity of 89.7% and a specificity
of 84.1% for delirium.^38^ The area under
the receiver operating characteristic (ROC) curves for delirium diagnosis was
0.93. Since the 4AT was launched, locally and through the www.the4AT.com website,
it has been adopted in clinical units in several centres in the UK and
internationally.

Thus, in 2014, there was encouraging evidence that the 4AT has value as a tool for
delirium detection in routine practice. This evidence came from several sources: one
published study, audits in several sites, informal feedback, adoption in clinical
practice by several clinical units globally and a recent web-based survey focused
specifically on 4AT provided evidence supporting its use. Since this study was
designed, other validation studies have been published, with favourable results;
however, these included specific clinical populations (eg, stroke^39^), languages (Thai^40^) had relatively small numbers^41^ or validated assessments against clinical assessment rather than
research reference standard assessment.^42^
Therefore, a formal, large validation study is necessary to provide definitive
evidence of the diagnostic accuracy of the 4AT.

Comparison with the CAM is also of value, because the CAM is in use in some clinical
units and thus information on how the 4AT performs in relation to the CAM will help
clinicians decide which tool is suitable for their particular context. Further
information on how the 4AT performs as a cognitive screening tool, its ability to
predict outcomes and how each item of the 4AT contributes to its diagnostic accuracy
will also provide important guidance to clinicians. Finally, understanding the
economic costs and benefits of using the 4AT and the CAM will help providers in
service pathway decisions.

### Study objectives

The *primary objective* of the study is to determine the diagnostic
accuracy of the 4AT for delirium detection versus the reference standard of a DSM-IV
diagnosis.

The *secondary objectives* are:to compare performance of the 4AT and the CAM;to determine if the 4AT is an adequately sensitive tool for detecting
general cognitive impairment as judged against a documented history of
dementia and/or the Informant Questionnaire for Cognitive Decline in the
Elderly (IQCODE);to determine if 4AT scores predict important outcomes such as length of
stay, institutionalisation and mortality up to 12 weeks;to determine the performance of individual items of the 4AT,
for example, how accurate is altered level of alertness alone as a
predictor of delirium diagnosis?to assess the 4AT total score as a measure of delirium severity;to estimate the delivery costs of the 4AT and CAM as a function of their
diagnostic performance up to 12 weeks as well as modelling longer term
resource consequences.

## Methods and analysis

### Study overview

Nine hundred patients aged 70 or over in EDs or acute general medical wards
will be recruited in three sites (Edinburgh, Bradford and Sheffield). Study
recruitment commenced on 19 October 2015. Recruitment was planned to be
completed in December 2016, with final follow-up data collection and locking of the
database in March 2017. The assessments are: (a) a reference standard delirium
assessment lasting up to 20 min and (b) either the 4AT or the CAM lasting up
to 10 min. The reference standard and 4AT or CAM assessments will take place
within a maximum of 2 hours of each other, with a target interval of
15 min. The results of the reference standard assessment were recorded in the
case notes and communicated to the clinical team after the index assessments had been
completed and recorded. The team will invite an appropriate informant to complete a
questionnaire on participant’s preadmission cognitive function. This will be
completed within 4 weeks of the patient being recruited to the study assuming an
appropriate individual is available.

At 12 weeks, the team will also administer a 10 min resource-use questionnaire
(face to face in hospitalised patients or by telephone when possible) and will access
each recruited patient’s medical records at 12 weeks to ascertain a set of key
clinical outcomes, including length of stay, institutionalisation and mortality, as
well as to derive further information on resource utilisation. The study
flow chart is shown in figure 1. The study has been registered: international standard randomised
controlled trial number (ISRCTN) 53388093. UK Clinical Research Network ID:
19 502.

**Figure 1 F1:**
[figure not shown]
Study overview flow chart. CAM, Confusion Assessment Method; ED, emergency
department; MOE, Medicine of the Elderly;
4AT, 4A's Test.

### Inclusion criteria

Aged 70 or over.Acutely admitted to the ED (within 12 hours of attending) or acute
general medical and geriatrics units (within 96 hours of admission to
the ward). For ED patients, we will only recruit from those patients who were
brought in by ambulance as an emergency or through their general
practitioner.

### Exclusion criteria

Acute life-threatening illness requiring time-critical intervention, for
example, ST-elevation myocardial infarction, septic shock and severe
pulmonary oedema.Coma (‘Unresponsive’ on the AVPU scale^43^).Unable to communicate in English or severe dysphasia.

### Identification of participants

The participant screening strategy in the initial protocol stated that patients will
be recruited between 08.00 and 22.00. A list of potentially eligible patients will be
generated in batches at the start of each recruitment period and initial eligibility
screening will be carried out by clinical staff (including clinical research nurses
embedded in the clinical team). Then, in alphabetical order, in each batch,
consent/agreement from patient (or proxy/consultee) will be sought by a study
researcher. Numbers of those (a) initially potentially eligible, (b) screened as
non-eligible by clinical staff and (c) declining to take part will be recorded.

This recruitment strategy was modified in the last 5 months of recruitment because
preliminary analyses suggested that patients at lower risk of delirium (ie, those not
requiring capacity assessment) were more likely to be recruited than those with
impaired capacity. Thus, to allow for some oversampling of patients at higher risk of
delirium, a pragmatic approach was adopted. From the batches of patients identified
as in the original strategy, patients considered at higher risk of delirium on
clinical grounds (eg, older age, likely to be admitted, higher degree of ongoing
acute and chronic illnesses) were approached first, rather than by alphabetical
order.

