### Lack of capacity to consent

It is essential that this study recruits patients which reflect the target clinical
population. This means that we must recruit patients with delirium in the same
proportion as in the clinical population. We will seek consent/agreement from legal
proxies, consultees or other legal representatives. Where the potential participant
is deemed to lack capacity to consent, recruitment will proceed under the provisions
of the Mental Capacity Act, 2005 in England or Adults with Incapacity (Scotland) Act,
2000. The clinical team will be asked to identify an appropriate personal or
nominated consultee, guardian, welfare attorney or nearest relative.

Because of differing legal requirements in Scotland and England, the details of the
processes in each nation are given in online Supplementary appendix 1.

10.1136/bmjopen-2016-015572.supp1Supplementary Appendix 1

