#### Primary objective

(a) 4AT versus reference standard: the diagnostic accuracy of 4AT versus
the reference standard will be assessed using positive and negative predictive
values, sensitivity and specificity. The exact binomial 95% CI will be reported
for each measure. A ROC curve will be constructed to verify that the proposed cut
point of greater than 3 on the 4AT score is appropriate. The area under the ROC
curve and its 95% CI will be reported.

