#### Secondary objectives

4AT versus CAM: differences in each of sensitivity, specificity, positive
and negative predictive values between 4AT and CAM will be tested by
Fisher’s exact test and quantified by the difference in the two
proportions (4AT-CAM) and its 95% CI. To aid comparison of 4AT and CAM, the
overall performance of each will also be summarised using Youden’s
Index (sensitivity minus false positive rate) and the OR of sensitivity to
specificity.Performance of the 4AT cognitive screening items: Is the 4AT an adequately
sensitive tool for detecting general cognitive impairment as judged against
a documented history of dementia and/or the IQCODE? This objective will be
addressed using the same methods as for the primary objective.4AT versus clinical outcomes: as assessment of criterion validity, we will
assess the performance of the 4AT in predicting length of stay,
institutionalisation and mortality up to 12 weeks. Descriptive
statistics of clinical outcomes will be presented for the groups with and
without 4AT scores above the cut point of 3. The relationship between 4AT
and each of mortality and institutionalisation will be analysed via logistic
regression modelling; Kaplan-Meier curves and the Cox proportional hazards
model will be used to assess 4AT as a predictor of hospital length of stay.
The logistic regression and Cox models will adjust for age, gender and
presence of dementia.Individual items: we will conduct analyses examining performance of
individual items of the 4AT, for example, is altered level of
alertness alone a good predictor of delirium diagnosis? (methods as per
primary objective);Delirium severity: we will assess the 4AT total score as a measure of
delirium severity by calculating the Spearman correlation between 4AT and
DRS-R98 scores and its 95% CI.

Full details of the proposed statistical analyses for the primary objective and
secondary objectives (a)–(e) will be documented in a SAP which will include
details of methods for calculating derived variables, any sensitivity and subgroup
analyses and approaches to testing the assumptions in the statistical analyses.
The SAP will outline the plan for validation of the statistical analysis.

Individuals with missing data for the reference diagnostic test will be removed
from formal statistical analysis. Where any items of the CAM or 4AT were not able
to be assessed, an overall delirium diagnosis will still be derived where possible

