## Discussion

This study was designed to validate the 4AT against a reference standard assessment, as
well as compare it with another commonly used test for assessment of delirium. Since the
initial study design, the 4AT has been widely adopted nationally and internationally.
The 4AT has been incorporated into routine practice in multiple international centres,
both in paper and electronic format, with many centres reporting 10 000 uses of
the tool. The website www.the4AT.com has had an increasing degree of traffic, and the 4AT has
been translated into multiple languages. The 4AT is also included in several national
guidelines and position statements internationally as a recommended tool and it has been
validated in other studies^38–42^ but it is still essential that it is further tested in a large
study. It is also essential to consider how well it identifies other types of cognitive
impairment, relates to future outcomes and its health economic impact.

In the initial design and implementation of the study, the main challenging aspects have
been: (1) considering both Scottish and English legal and ethical framework to ensure
that patients without capacity are included. Ethical approval for inclusion of these
patients was granted though recruitment of this patient group proved difficult from the
outset for several reasons. First, the narrow boundaries for the screening and
identification strategy. This was addressed in a subsequent protocol amendment to aim
for oversampling of patients at risk of developing delirium. Second, the availability of
an appropriate individual to provide consent on behalf of the participant (ie, a
personal or nominated consultee, guardian, welfare attorney or nearest relative). Third,
a reluctance to consent due to perceived burden on participant. Persuading relatives of
the value, importance and necessity of research even in clinically unwell patients
demands a particular skillset from researchers and involved perseverance and excellent
communication in order to achieve recruitment targets.

(2) Recruitment and training of staff, with some staff moving to different posts,
and new staff being recruited and requiring training; in each case, detailed training
supported by reading materials and practice sessions was provided.

We also acknowledge that it is possible that researcher bias may influence how the
different index assessments (4AT or CAM) were scored. We also acknowledge that given the

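### Higher-risk patients were deliberately oversampled late in recruitment, so the raw pooled PPV and NPV describe the study sample and cannot be read as clinical predictive values

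*Protocol article*

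**What the plan says.** Protocol article, *Identification of participants*: patients were at first approached alphabetically within batches. "This recruitment strategy was modified in the last 5 months of recruitment because" "preliminary analyses suggested that patients at lower risk of delirium" were being recruited more readily than those with impaired capacity. From then on, patients thought to be at higher risk on clinical grounds "were approached first, rather than by alphabetical" order. The stated purpose was "to allow for some oversampling of patients at higher risk of" delirium. The *Discussion* confirms that a protocol amendment aimed "for oversampling of patients at risk of developing delirium".

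*Lack of capacity to consent* sets a different requirement: "This means that we must recruit patients with delirium in the same" proportion as is found in the clinical population.

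*Primary objective*: the accuracy of the 4AT against "the reference standard will be assessed using positive and negative predictive" values together with sensitivity and specificity, each with an exact binomial 95% CI. *Secondary objectives*: for 4AT against CAM, "differences in each of sensitivity, specificity, positive" and negative predictive value are tested by Fisher's exact test and given as differences with 95% CIs.

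Neither analysis section mentions the change of approach order. The one limitation on sample selection in *Strengths and limitations* concerns consent.

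**The concern.** PPV and NPV depend directly on prevalence. A raw proportion among test positives or test negatives estimates the clinical value only if the sample carries delirium at its clinical prevalence. The article states that condition in one section and describes a deliberate departure from it in another.

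The sample is a mixture of two recruitment schemes. In the first, lower-risk patients were over-represented. In the second, higher-risk patients were put first by clinical judgement. Neither has known selection probabilities. The counts that the article says will be logged (potentially eligible, screened out, declined) do not, as described, record risk or delirium status, so they would not allow the sample to be reweighted.

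An exact binomial interval expresses sampling error around whatever PPV the mixture happens to have. It says nothing about the distance between that PPV and the one a ward or emergency department would see. Clinicians read PPV directly, and it is among the primary accuracy measures.

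**Working it through.** **Inputs.** Per arm: 450 patients, 15% (67) with delirium and 383 without (*Sample size calculation*). Illustrative accuracy: sensitivity 0.897 and specificity 0.841 (the Italian validation study cited in *Rationale for the study*). Enriched period: the last 5 months. Recruitment length: 19 October 2015 to December 2016, about 14.5 months (*Study overview*), or 18 months (*Abstract*). The documents give neither the achieved nor the clinical prevalence, so prevalence is an assumption, shown as a range.

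**The plan's own figures.** Half-width = 1.96·√(p(1−p)/n).
- n = 383: 0.0501, 0.0459 and 0.0300 at p = 0.5, 0.7 and 0.9.
- n = 67: 0.1197, 0.1097 and 0.0718.

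Table 1 is reproduced.

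**Predictive values by prevalence π**, with sensitivity (se) and specificity (sp) held fixed:

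PPV = se·π / [se·π + (1−sp)(1−π)]

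NPV = sp(1−π) / [sp(1−π) + (1−se)π]

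At π = 0.15: PPV = 0.13455 / (0.13455 + 0.13515) = 0.499.

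At π = 0.20: PPV = 0.1794 / (0.1794 + 0.1272) = 0.585.

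| Prevalence | PPV | NPV |
|---|---|---|
| 10% | 0.385 | 0.987 |
| 15% | 0.499 | 0.979 |
| 20% | 0.585 | 0.970 |
| 25% | 0.653 | 0.961 |
| 30% | 0.707 | 0.950 |

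**Against planned precision.** At 15% prevalence, expected test positives are 450 × 0.2697 = 121.4. The PPV half-width is 1.96·√(0.499 × 0.501 / 121.4) = 0.089. A move from 15% to 20% shifts PPV by 0.585 − 0.499 = 0.086, just under one half-width. NPV falls from 0.979 to 0.970.

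**What the mixture could do.** With even accrual (an assumption), the enriched share is 5/14.5 = 0.345, or 5/18 = 0.278.
- 15% before and 30% after the change: 0.655 × 0.15 + 0.345 × 0.30 = 20.2% pooled, PPV 0.588. Over 18 months: 19.2%, PPV 0.572.
- 10% before and 25% after: 0.655 × 0.10 + 0.345 × 0.25 = 15.2% pooled, PPV 0.502. Over 18 months: 14.2%, PPV 0.482.

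The same 15-point rise in the late period can leave the pooled figure well above 15% or almost on it. The outcome depends on how far the early period fell short, which is not documented.

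**The case against.** The strongest reply is that the change was corrective. Lower-risk patients had been over-represented, so approaching higher-risk patients first may have brought the pooled prevalence closer to the clinical one. This stands. A reader might infer that PPV will be inflated, or that the sample prevalence matches no real clinic; the documents support neither. They do show that nothing calibrated the correction, so closeness to clinical prevalence cannot be assumed either.

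The size also has limits. A pooled shift of 5 points from the early-period level needs a late-period prevalence about 14.5 points higher (5/0.345), or 18 points (5/0.278) over the longer recruitment period. The article speaks only of some oversampling. The NPV effect is small in absolute terms.

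A reader might also infer that the 4AT–CAM comparison is compromised. It is not. Patients were randomised 1:1 within site and both arms share the same recruitment mix, so the change does not confound the contrast. Nor does chance imbalance in delirium between arms add a separate error. Given the number of test positives, true positives are binomial with probability PPV, so that variation is already inside the ordinary sampling error. What remains is that the size of a PPV or NPV difference depends on the prevalence at which it is evaluated.

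Finally, the article leaves sensitivity and subgroup analyses to an SAP that is not at hand, so the absence of a by-period analysis here is not a fault. The point rests on what the article does fix: the raw estimator, alongside a sampling change that conflicts with its own stated requirement.

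**Conclusion.** The point holds as a matter of estimation and interpretation for PPV and NPV, and it should be fixed. As planned, these are sample-specific quantities at a prevalence set partly by approach order, and their exact intervals do not cover that source of uncertainty. For PPV, a 5-point prevalence discrepancy around the planning value is worth about one planned half-width; for NPV it is worth about 0.01.

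These sizes assume the cited sensitivity and specificity and that both stay constant as prevalence changes. The actual discrepancy and its direction are unknown.

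The conclusion does not extend to sensitivity and specificity, which do not depend directly on prevalence and on which the precision table is built. A changed case mix could in principle shift them, but no figure in the document shows that it did.

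**What to change.** 1. Reconcile *Identification of participants* with *Lack of capacity to consent*, so that the article no longer both requires the clinical proportion and describes oversampling without comment. Add the change of approach order to the stated limitations.
2. Keep the raw PPV and NPV with exact CIs, labelled as applying to the study sample.
3. Report PPV and NPV for both tests by Bayes' rule from the estimated sensitivity and specificity, over a common pre-specified prevalence range (for example 10–30%), with delta-method or bootstrap CIs. Give the 4AT–CAM differences at the same prevalences. Include the 15% planning value but do not make it the sole headline: *Background* gives 15% as a minimum for acute hospitals and says delirium is more common in older people, and this study enrols only those aged 70 or over.
4. Show accuracy separately for the alphabetical and risk-ordered periods as a descriptive check only. With even accrual, the late period would hold about 67 × 0.345 ≈ 23 delirium cases per arm at the planning prevalence, giving a sensitivity half-width of 1.96·√(0.9 × 0.1 / 23) ≈ 0.12 at a sensitivity of 0.9.

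The cost is SAP wording, ideally settled before database lock, and a few lines of code; no new data are needed. The downside is small: the added predictive values are model-based and assume that sensitivity and specificity are constant across prevalence.
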